### Data collection

3.3

Participants will be asked to complete a series of web-based surveys at baseline, six weeks and 12 weeks. These surveys include validated scales and objective questions on COVID-19 infection and medical history. The validated questionnaires assess stress, mood states, resilience, and overall wellbeing. Questionnaires, weekly activity diaries, and medical history, will be collected using REDCap. All surveys will all be automated and the study team will have minimal interaction with the participants. All health information provided by the participants is self-reported.

### Measures

3.4

Each participant will be asked to respond to 8 validated neuropsychological scales assessing stress (Perceived Stress Scale, PSS), anxiety and depression (PHQ-4), joy predisposition (DPES-Joy Subscale), mindfulness awareness (MAAS), resilience (BRS), mental well-being (WEMWBS), and post-traumatic growth (PTGI). PSS is defined as the primary outcome while BRS is the key secondary outcome.

**Questionnaires**. The following questionnaires are incorporated into the study survey and will be administered to the study participants:

*Perceived Stress Scale (PSS).* PSS is a 10-question validated instrument that assesses stress. Participants are asked to rate on a scale of 0 (never) to 4 (very often) how often they agree with various statements designed to assess the degree to which life situations are appraised as stressful. Items from each of the 10 questions are then summed to create a total perceived stress score.

*4 Item-Patient Health Questionnaire measuring Anxiety and Depression (PHQ-4).* Four questions rated on a scale of 0 (Not at all) to 3 (Nearly every day). The sum is computed for the responses and scores range from 0 to 12. Categories of psychological distress are classified as: None (0–2 score), Mild (3–5 score), Moderate (6–8 score) and severe (9–12 score). Anxiety subscale is calculated by measuring sum of item 1 and 2 (score range, 0–6; scores greater than 3 considered positive for anxiety screening.) Depression subscale is calculated by measuring sum of item 3 and 4 (score range, 0–6; scores greater than 3 considered positive for depression screening.)

*Dispositional Positive Emotion Scale- Joy Subscale (DPES-Joy).* The joy subscale of DPES is a 6-item questionnaire that measures a dispositional tendency to feel joy in life. Participants report their level of agreement to each item on a scale of 1 (Strongly agree) to 7 (Strongly disagree) and a mean score is calculated.

*Mindfulness Attention Awareness Scale (MAAS)- short form.* MAAS - short form is a 5-question validated instrument that assesses mindfulness and attention while performing routine activities of daily living. Participants are asked to rate on a scale of 1 (Almost Always) to 6 (Almost Never) the frequency of occurrence for each experience. A mean score is then computed using items from each of the 5 questions to calculate the individual's MAAS score.

*Brief Resilience scale (BRS).* The BRS identifies an individual's ability to “bounce back” or recover from a stress. This 6-item scale is rated on a 5-point response scale (1 = Strongly disagree; 5 = Strongly agree). Responses from each of the 6 questions are summed to create a total score, producing a range of 6–30. The score is divided by the number of questions answered to calculate the individual brief resilience score.

*Warwick- Edinburgh Wellbeing Scale (WEMWBS).* The purpose of the WEMBS scale is to assess various aspects of mental health such as positive affect, satisfying interpersonal relationships, and positive functioning. This 14-item scale is rated on a 4-point response scale (1 = none of the time to 4 = all of the time). Response from each of the 6 questions is then summed to create a total wellbeing score.

*Post Traumatic Growth Inventory (PTGI).* The purpose of the PTGI is to capture the positive outcomes reported by a person who has experienced a traumatic event. This scale will be administered only to those participants who report being hospitalized during the COVID-19 pandemic. The scale helps to determine a respondent's coping ability in the aftermath of a trauma, their perceptions of self and others, and meaning of the event. This 21-item scale is rated on a 6-point Likert response scale and response to each question is summed to create a total PTGI score.

*Activity Diary.* The weekly activity diary is a tool which helps the participants to keep a track of their activities each week. This enables the study team to measure compliance and protocol adherence by the participants. Based on the construct of the study, we have 2 different activity diaries employed for data collection in this study. The activity diary for seasoned yoga practitioners collects information on their routine activity practiced, its frequency and duration. The activity diary for controls collects information on the activity suggested by study team (the Simha Kriya yoga practice vs placebo activity choices of reading or remaining idle).

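### The WEMWBS is described as a 14-item scale, but its scoring sentence sums 6 questions; the item count in the rule needs to be reconciled

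*Protocol article*

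**What the plan says.** Section 3.4 (Measures) gives each instrument its number of items, its response options and its scoring rule. For the WEMWBS, the description is "This 14-item scale is rated on a 4-point response scale", with responses coded 1 to 4. The scoring rule follows at once: "Response from each of the 6 questions is then summed to create a total wellbeing score". No range is given for the total.

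The paragraph before it covers the BRS, a six-item scale coded 1 to 5, and reads "Responses from each of the 6 questions are summed to create a total score, producing a range of 6–30".

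On the rank of the outcomes, the same section states "PSS is defined as the primary outcome while BRS is the key secondary outcome". Wellbeing is one of the three constructs named in Specific Aim 1 (section 2) and again in the Aim 1 analysis (section 3.6). The list at the start of section 3.4 gives the WEMWBS as the mental well-being instrument.

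**The concern.** Two adjacent sentences give different item counts for the same score. This is a stated scoring rule for a named Aim 1 outcome, so it is neither background text nor a detail left to a fuller document. If a separate analysis plan gives the right rule, the article contradicts that plan.

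At stake is whether the wellbeing total is the total of the instrument described. A sum over six of fourteen items would be on a different scale and could not be set beside other 14-item totals. Section 3.3 says that the surveys are automated and collected in REDCap, so a scoring error made in code would apply to every participant at baseline, 6 weeks and 12 weeks. Because no range is printed, a reader has no second figure that would expose the slip, as there is for the BRS and the PHQ-4.

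**Working it through.** **Inputs**, all from section 3.4 of the protocol article:

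- WEMWBS: 14 items, coded 1 to 4, total formed from 6 questions.
- BRS: 6 items, coded 1 to 5, stated summed range 6 to 30.
- PHQ-4: 4 items, coded 0 to 3, stated summed range 0 to 12 ("The sum is computed for the responses and scores range from 0 to 12").

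**Formula.** The range of a summed score runs from (items × lowest code) to (items × highest code).

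**Step 1: reproduce the article's own ranges.**

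- BRS: 6 × 1 = 6 and 6 × 5 = 30, which matches.
- PHQ-4: 4 × 0 = 0 and 4 × 3 = 12, which matches.

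The formula is therefore the one the article uses.

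**Step 2: apply it to the WEMWBS at the stated coding.**

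- Six questions, as the scoring sentence says: 6 × 1 = 6 to 6 × 4 = 24.
- Fourteen items, as the description says: 14 × 1 = 14 to 14 × 4 = 56.
- Items unused under the literal rule: 14 − 6 = 8, and 8/14 = 57%.

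**Step 3: compare item counts across the section.**

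| Scale | Items described | Items in scoring rule |
|---|---|---|
| PSS | 10 | 10, summed |
| MAAS short form | 5 | 5, averaged |
| BRS | 6 | 6, summed |
| WEMWBS | 14 | 6, summed |
| PTGI | 21 | every question, summed |

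The PHQ-4 and the joy subscale give no separate count in the scoring rule, so they cannot conflict. The WEMWBS is the only mismatch. Its scoring sentence also closely follows the BRS sentence above it, including the count of six, which is correct for the BRS.

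**Step 4: look for text that would reconcile the two counts.** The article names no six-item subset and no short form of the WEMWBS, although it does identify the MAAS as a short form. Nothing in the objectives, the data collection section or the analysis section settles the matter.

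**The case against.** The strongest reply is that this is a copying slip with no consequence. The sentence does not say which six items to sum, so nobody could program it as written. The aims refer to validated scales, which suggests that the whole instrument was meant. Section 3.6 reports that the 12-week data had already been reviewed, so a change of wording alters no data collection. The WEMWBS is also neither the primary nor the key secondary outcome.

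Most of this stands. Carried-over wording is the likeliest explanation, and the reach is limited to one Aim 1 measure. But a probable explanation is not a resolution: the article still states a rule that conflicts with its own description and does not show which count the scoring code used. That the data are in hand does not make the point idle, since code can still be checked and stored item responses summed again.

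Three stronger readings are tempting, and the document supports none of them.

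- **A reader might infer that a stated range is wrong.** No WEMWBS range is printed. Both 6 to 24 and 14 to 56 are derived here from the item counts and the stated coding.
- **A reader might infer that eight items were in fact dropped from the score.** The article does not show how the totals were computed, and the likely origin of the sentence points the other way.
- **A reader might infer a loss of reliability and power, and a need for more participants.** That would require an assumed reliability that the article does not give, interchangeable items, and actual six-item scoring. The article shown also sizes nothing on the WEMWBS, so no stated figure would change.

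**Conclusion.** The point holds as an internal contradiction: 14 items in the description against 6 in the scoring rule. That much rests on the article's text alone and needs no assumption. Taken literally, the rule would omit 8 of 14 items and produce something other than the total of the instrument described.

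The derived ranges (6 to 24 against 14 to 56) depend on the 1 to 4 coding. That coding stands in the same paragraph as the slip, with no printed range to check it against, so it should be confirmed before it is relied on.

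The consequence is confined to the wellbeing total under Aim 1. The PSS and BRS definitions, and any conclusion drawn from them, do not depend on this sentence. It should be corrected because the rule is wrong as written and correction is nearly free, not because harm to the results has been shown.

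**What to change.** 1. **Correct the item count.** State that the responses to all 14 questions are summed. If a six-item subset was intended, name the items and say that the score is not the 14-item total.
2. **Confirm the response coding** against the questionnaire as administered, then print the range: 14 to 56 if all 14 items are used and the 1 to 4 coding is right.
3. **Check that the scoring code sums all 14 items.** A quick first screen, if the 1 to 4 coding is confirmed: any recorded total above 24 cannot come from six items, and any total below 14 cannot come from a complete set of fourteen. Totals from 14 to 24 fit both rules, so the code itself still has to be read. If six items were summed without intent, recompute from the stored item responses.

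The cost is one corrected sentence and a short check of code and questionnaire. No new data are needed, and no other outcome is affected.

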### Randomization

3.5

Non-meditators or control arm participants will be randomized into one of the two groups using the REDCap Block Randomization Technique. Participants will be randomized into one of two groups:1)Active Comparator: Participants will be taught the 3 min Simha Kriya practice which involves deep breathing exercises with meditation (twice daily) for the study duration (12 weeks).2)Placebo Comparator: Participants can choose to either read a book of their choice or stay idle for 15 min each day for a total duration of 12 weeks.

### Analysis

3.6

Baseline characteristics of participants will be recorded. Continuous data will be presented as means ± standard deviation or median (interquartile range) depending on the distribution of the data and assessed with a parametric paired *t*-test or non-parametric Wilcoxon signed rank test, as appropriate. Normality will be assessed with the Shapiro-Wilk test. Categorical data will be presented as frequencies and percentages and assessed with a chi-square or Fisher's exact test, as appropriate. All primary analyses will be assessed using intention-to-treat principles. SAS 9.4 (SAS Institute Inc., Cary, NC) will be used for all analyses with two-sided p-values < 0.05 considered statistically significant.

Aim 1 Analysis. To quantitatively assess the effects of Isha yoga practices between seasoned practitioners and the control groups on measures such as perceived stress, resilience, and overall wellbeing by use of validated scales at baseline, 6 weeks and 12 weeks. We have defined Perceived Stress Score as our primary outcome and Brief Resilience Scale scores as our key secondary outcome. Given the continuous nature of the scales used to assess stress, resilience and measures of well-being, differences between groups will be assessed with a parametric or non-parametric *t*-test. Multivariable regression may be utilized to adjust for potential confounders that deem to vary between the groups based on the univariable analysis prior to that. The distribution of the dependent variable will depend on the actual distribution of the scales recorded in the study. A mixed effect approach in modeling will address the similarity of the subjects enrolled in the study as friends or by matching, by assigning a random intercept to each cluster of related subjects. To assess whether there are differences between baseline and at six weeks, we will employ the use of paired t-tests or non-parametric tests for univariable analysis, as appropriate. Additionally, the change in scales over time can be compared between the groups using mixed models approach, wherein an indicator of time (baseline/6 weeks) will define the direction and significance of the change in a model, adjusted independent of other factors.

Aim 2 Analysis. To Compare Protection and Recovery from COVID 19 infection between seasoned Isha yoga practitioners and controls as demonstrated by:a.Self-reported duration of fever and respiratory symptoms in COVID-19 positive participantsb.Self-reported readiness to return to work (or a feeling of being physically and mentally fit)

We will calculate the protection and recovery rates from COVID-19 infection as defined by the aforementioned criteria. Given the continuous nature of the criteria used to assess symptom duration and sense of recovery, differences between groups will be assessed in a univariable manner with a parametric or non-parametric *t*-test. We will perform spot analysis at the three defined points to capture the point prevalence of recovery rates. We also intend to assess the differences between the prevention and recovery rates at baseline and six weeks and baseline and twelve weeks. We will employ the mixed model technique similarly to the analysis suggested in the aim #1 analysis.

Analysis of Aim 3: To compare Prevalence rates of diagnosed COVID-19 infection between the seasoned Isha yoga practitioners and age and gender matched controls at baseline, 6 weeks, and 12 weeks.

We will compute period prevalence of diagnosed COVID-19 infections as a measure of frequency. Since the data to be analyzed are not dependent on duration, we intend to compute the prevalence rates at the following time points: baseline, 6 weeks, and 12 weeks. The result would be reported as the portion of study population with COVID-19 at the specified time point.

Finally, we will perform an exploratory analysis of the data collected by comparing the effect of yoga practices and their duration between the 3 study groups to estimate a dose-response trend if possible.

Compliance is defined as 3 days of activity each week for at least 3 weeks from baseline to 6 weeks, or a minimum of 6 weeks from baseline to 12 weeks. Measures of frequency and association will also be calculated. We will complete exploratory analysis by comparing the different yoga practices and their duration between the 3 study groups to assess a dose-response pattern.

After reviewing the data that was collected over the 12 week period, several amendments were made to the protocol. For example, we compared the three groups, Group 1: Simha-Kriya Yoga for a period of 12 weeks, Group 2: Reading activity/Sitting idle for a period of 12 weeks, and the Yoga Practitioners, rather than the combination of control groups with the yoga practitioners. We also performed Poisson regression rather than linear regression to account for potential confounders due to the distribution of the primary outcomes, PSS and BRS scores. These changes were towards a more conservative approach which we believe provided more valid inference.

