### Participant recruitment

3.1

We will employ a two-stage recruitment design. First, seasoned yoga participants will be recruited by social media, websites, flyers, word of mouth, email announcements at the Isha Foundation [30], an international school of yoga. Seasoned yoga participants are defined as individuals who have completed at least one, in-person yoga Isha Yoga training protocol with an Isha yoga trainer and are regularly doing the practice. The Isha Foundation will facilitate this stage of the recruitment by including study recruitment flyers and links to its broad follower base of meditators and yoga practitioners. These communications will have a survey link where prospective participants can confirm their interest in the study and learn more detailed information about study procedures. They will then be directed to a brief REDCap survey where they will be asked screening questions to ensure study eligibility. Those who are eligible will be directed to an electronic consent form and enrolled in the study following the submission of the consent agreement.

The second stage of the recruitment uses snow-ball sampling [31]. Following enrollment in the study, seasoned yoga practitioners are requested to nominate two friends who can act as age and gender matched controls, preferably living in the same neighborhood. The study team will reach out to the nominated individuals to describe the study, assess interest and eligibility, and direct prospective respondents to an electronic consent form specific for the control groups. Respondents will be enrolled following the provision of their consent.

The process of nominating controls for the study is voluntary and seasoned yoga practitioners can participate without referring any controls. In this situation, unmatched controls and practitioners will be matched by the study team based on their self-reported location details. The team prioritizes matching the zip codes followed by town, city, county, and state.

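### The general rule in section 3.6 names only paired tests for continuous data, which do not fit between-group comparisons in a design of variable-size matched sets and three groups

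*Protocol article*

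**What the plan says.** **General rule (protocol article, section 3.6, opening paragraph).** Directly after the sentence on baseline characteristics, continuous data are to be summarised by mean or median "depending on the distribution of the data and assessed with a parametric paired" t-test or "non-parametric Wilcoxon signed rank test, as appropriate". Both are tests for paired observations. For the other variable type the same paragraph says: "Categorical data will be presented as frequencies and percentages and assessed with a chi-square" or Fisher's exact test. Those are tests for independent groups. The threshold is set "with two-sided p-values < 0.05 considered statistically significant".

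**Design (section 3.1).** After enrolling, "seasoned yoga practitioners are requested to nominate two friends who can act as age and gender matched controls". Nomination is voluntary: "seasoned yoga practitioners can participate without referring any controls". There is a fallback: "unmatched controls and practitioners will be matched by the study team based on their self-reported location details".

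**Allocation and groups.** Section 3.5 block-randomises the controls to two arms and states no randomisation within a matched set. The closing paragraph of section 3.6 reports that three groups were compared instead of practitioners against the combined controls.

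**Aim 1 (section 3.6).** Group differences on the scales are to be tested with a parametric or non-parametric t-test, without saying paired or unpaired. Regression is optional and may adjust for "potential confounders that deem to vary between the groups based on the univariable analysis". A mixed model gives each cluster of related participants a random intercept. Paired t-tests for baseline against six weeks have their own sentence.

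**The concern.** A paired test needs each observation in one group to have exactly one partner in the other. Here a set holds one practitioner and up to two controls, those controls may fall in the same arm or in different arms, and active and placebo participants are not partnered by design. No single paired t-test or signed-rank test compares three groups. The same paragraph also treats the same people as independent when the variable is categorical.

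An analyst who follows the rule for a between-group comparison has to improvise: drop participants to make pairs, use a practitioner twice, or pair people arbitrarily. These choices differ in error rate and precision, and the article does not choose among them. At stake are the baseline and univariable p-values, and possibly the choice of adjustment covariates if those p-values serve as the screen.

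**Working it through.** The article gives no sample size, effect size or power, so there is no plan figure to reproduce.

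**Inputs from the article:** two-sided alpha 0.05 (section 3.6); two controls requested per practitioner (3.1); controls randomised to two arms with no stated link to the set (3.5); three groups (3.6, closing paragraph).

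**Assumptions:** complete sets of one practitioner (P) and two controls (C1, C2); common variance v; within-set correlation rho; controls split 1:1 between arms independently of set. Simulations used 50, 100 and 200 sets, rho of 0, 0.1 and 0.3, and 5,000 runs per setting.

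**1. One pair per set, against pooled controls.**
- Var(P − C1) = 2v(1 − rho)
- Var(P − mean of C1 and C2) = v + v(1 + rho)/2 − 2·rho·v = 1.5v(1 − rho)
- Ratio = 2/1.5 = 1.33 for any rho

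Simulated alpha with one pair per set was 0.044 to 0.052, so the error rate holds. The cost is half of the controls.

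**2. Practitioner used in two pairs.**
- Cov(P − C1, P − C2) = v − 2·rho·v + rho·v = v(1 − rho)
- Correlation of the two differences = v(1 − rho) / [2v(1 − rho)] = 0.5 for any rho
- The test takes them as independent, so it understates the variance of the mean difference by a factor of 1 + 0.5 = 1.5
- True two-sided alpha = 2[1 − Phi(1.96/√1.5)] = 2[1 − Phi(1.60)] = 0.110

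Simulated alpha was 0.104 to 0.117.

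**3. By arm.**
- Practitioner against active: a set has at least one active control with probability 1 − 0.5² = 0.75, so about 25% of practitioners have no partner (simulated 0.751 to 0.753 kept).
- Active against placebo: a set has one control in each arm with probability 2 × 0.5 × 0.5 = 0.50, so about half of the randomised controls are lost (simulated 0.501 to 0.506 kept).

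The block size is not given. If friends were randomised together in small blocks, these fractions would differ.

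**4. Illustration of the loss** (assumed difference 0.4 SD, 100 complete sets, independent observations; not trial figures).

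| Comparison | All participants | Forced pairs |
|---|---|---|
| Practitioners vs pooled controls | 100 vs 200: 90% power | 100 vs 100: 81% |
| Active vs placebo | 100 vs 100: 81% power | about 50 pairs: 52% |

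**5. Can the sentence mean within-person change?** Not for baseline characteristics, which have no second measurement to pair with. Within-person change is also covered by the separate Aim 1 sentence on baseline against six weeks.

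**The case against.** **The primary comparison has its own rule.** Aim 1 does not call its between-group test paired, and the mixed model handles related participants through a random intercept. This stands: the defect does not touch that model. A reader might go further and see a flat contradiction between a paired general rule and a two-sample Aim 1 test. The article does not support that, because Aim 1 does not say which kind of t-test it means.

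**Matching does exist.** This also stands. A reader might infer that pairing is simply unavailable, or that every practitioner without a nominee would be lost. The location matching by the study team rules out the second inference; only practitioners whom the team cannot match would be lost, and that number is not given. The exact statement is matched sets, not pairs.

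**The test is not always invalid.** True. One pair per set keeps alpha near 0.05. The rise to about 0.11 needs a practitioner to be used twice, which the article does not propose.

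**The factor 1.33 has a narrow scope.** True. It applies to a practitioner against two pooled controls. In the three-group comparison, a set whose controls fall in different arms has no second control to drop from a practitioner-versus-arm contrast.

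**The paragraph is general, and this is a condensed article.** The paragraph also covers normality testing, intention-to-treat and software, and the later paired sentence could be an application of it. That makes the wording look like a slip, but does not repair it: for continuous data it names paired tests only, immediately after baseline characteristics. This is a stated rule that does not fit the design, not a detail left to another document.

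**Conclusion.** The point holds in limited form. As written, the general rule for continuous data does not fit between-group comparisons in this design. Depending on how pairs are forced, it costs participants (variance ratio 1.33 against pooled controls; about 25% of practitioners or half of the controls in by-arm contrasts) or roughly doubles two-sided alpha, to about 0.11. These figures assume complete sets of three and 1:1 allocation independent of set; 1.33 and 0.11 do not depend on the within-set correlation.

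The reach is the baseline and univariable comparisons. A reader might conclude that the error carries into the adjusted PSS and BRS results. The closing paragraph of section 3.6 does report Poisson regression to account for confounders, and the paired rule is the only test that the article names for continuous characteristics. But Aim 1 makes regression optional and does not identify its univariable screen with the tests of the opening paragraph. The link is plausible, not stated. The correction should be made, but it does not call the planned random-intercept model into question.

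**What to change.** Amend section 3.6 as follows:

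- Restrict the paired t-test and the signed-rank test to within-person change.
- For between-group comparisons of continuous data, use the cluster random-intercept model already planned, with group as a three-level factor.
- Describe the baseline of the two randomised control arms without significance tests.
- Choose adjustment covariates in advance on subject-matter grounds, not from univariable p-values.

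Since the article says that analyses were changed after the data had been reviewed, the report should also state which test was used for each between-group comparison and how the covariates were chosen.

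The cost is analysis wording only; no new data and no change to recruitment or randomisation are needed.

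### The test and effect measure for the primary outcome PSS (and for BRS) are left to the observed distribution, with a Shapiro-Wilk test as the only stated criterion

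*Protocol article*

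**What the plan says.** All of this is in section 3.6 (Analysis) of the protocol article unless noted.

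- **General paragraph.** Continuous data are summarised and tested "depending on the distribution of the data and assessed with a parametric paired *t*-test or non-parametric Wilcoxon signed rank test, as appropriate". The next sentence is "Normality will be assessed with the Shapiro-Wilk test". It gives no threshold and does not say which variable, group or time point is tested.
- **Aim 1, between groups.** "differences between groups will be assessed with a parametric or non-parametric *t*-test".
- **Aim 1, change from baseline to six weeks.** "we will employ the use of paired t-tests or non-parametric tests for univariable analysis, as appropriate".
- **Aim 1, regression.** "The distribution of the dependent variable will depend on the actual distribution of the scales recorded in the study". Adjusted regression is worded as optional. A mixed model with a random intercept per cluster of friends or matched subjects is proposed.
- **Closing paragraph on amendments.** After the 12-week data were reviewed, Poisson regression replaced linear regression, "due to the distribution of the primary outcomes, PSS and BRS scores".
- **Outcome status and scoring (section 3.4, Measures).** "PSS is defined as the primary outcome while BRS is the key secondary outcome". PSS has ten items scored 0 to 4: "Items from each of the 10 questions are then summed to create a total perceived stress score".

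**The concern.** A primary analysis should answer one question with one effect measure. Here the question depends on how the scores happen to be distributed. If a normality test passes, the result is a difference in mean PSS; if it fails, the result is a rank comparison. Six-week and 12-week results, PSS and BRS, or one pair of groups and another could therefore end up on different measures, and a reader could not set them side by side.

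A normality test also selects badly for a score of this kind. A sum of ten items is discrete and bounded, so it is never exactly normal, and whether the test detects that depends largely on the number of participants. The t-test is then kept in small samples, where non-normality matters most, and dropped in large ones, where it matters least.

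This is not a detail that an article simply leaves to an analysis plan. The text states a data-dependent choice for the primary outcome.

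**Working it through.** **Inputs from the document.** PSS is the sum of 10 items scored 0 to 4, so its range is 10 × 0 = 0 to 10 × 4 = 40, in whole numbers. Significance is two-sided at 0.05. The article gives no sample size, SD or expected difference, so there is no stated figure to reproduce.

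**Assumptions.** Scores are rounded and clipped to 0–40, with mean 16 and SD 6.5. Three shapes are used: rounded normal (skew about 0.05), skew 0.30 and skew 0.43. The selection rule is also assumed, because the article gives none: if Shapiro-Wilk has p < 0.05 in either group, use Mann-Whitney; otherwise use the t-test. Each cell has 4,000 runs (2,000 at n = 800).

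**Step 1. How often is the analysis moved to the rank test?** For exactly normal data and two groups the rate would be 1 − 0.95² = 9.75%. Simulated rates:

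| n per group | 25 | 50 | 100 | 200 | 400 | 800 |
|---|---|---|---|---|---|---|
| rounded normal | 10% | 10% | 11% | 19% | 48% | 100% |
| skew 0.30 | 16% | 23% | 38% | 67% | 97% | 100% |
| skew 0.43 | 21% | 36% | 64% | 92% | 100% | 100% |

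Each row is one population, so the change along a row is due to sample size alone. A different shape (rounded scaled beta, SD 7) shows the same pattern. At 50, 100 and 200 per arm, at least one arm fails in 48%, 90% and 100% of trials with mean 14 (skew 0.41), and in 16%, 34% and 78% with mean 18 (skew 0.13).

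**Step 2. Does the switch damage error control when group shapes match?** Over the 18 cells above, type I error was 4.1% to 5.5% for the t-test and 3.7% to 5.8% for the two-stage rule. The 95% simulation band around 5% is ±1.96 × √(0.05 × 0.95 / 4,000), about ±0.7 points (±1.0 point with 2,000 runs). There is no material inflation. There is also no gain: the t-test did not need replacing.

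**Step 3. What if shapes differ but means are equal?** Assumed: a gamma shape with SD 4 against a normal shape with SD 7, both with mean 16; 3,000 runs; Welch's t-test as the parametric option.

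| group sizes (SD 4 / SD 7) | Welch t | two-stage rule |
|---|---|---|
| 50 / 50 | 4.9% | 6.0% |
| 200 / 200 | 5.2% | 6.5% |
| 400 / 200 | 4.9% | 9.5% |
| 400 / 100 | 4.8% | 10.4% |

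Mann-Whitney tests whether the distributions are the same, so unequal spread and shape can make it reject when the means do not differ.

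**Step 4. Would any t-test do in Step 3?** No. With 400 / 100, the true variance of the difference is 16/400 + 49/100 = 0.53. A pooled-variance t-test uses about [(399 × 16 + 99 × 49) / 498] × (1/400 + 1/100) = 0.282. The standard error is too small by a factor of √(0.53 / 0.282) = 1.37, and the error rate is P(|Z| > 1.96 / 1.37), about 15%. What protects the comparison of means is a standard error that allows unequal spread, not the parametric label.

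**The case against.** Several points on the other side are fair.

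- **The link to PSS is a reading.** The Shapiro-Wilk sentence is in the general paragraph, beside paired tests and after a sentence on baseline characteristics. The Aim 1 paragraph does not mention it. A reader might infer that a failed Shapiro-Wilk test mechanically forces a rank test on PSS. The text does not say that: it gives no threshold and leaves room for judgement. What stands is that Aim 1 repeats the same either/or and that no other criterion is given anywhere.
- **The harm to error rates is small.** A reader might infer that type I error is generally inflated. Step 2 contradicts this for matching shapes. Power is not lost either: for a 2.5-point difference in the beta scenarios at 50, 100 and 200 per arm, the two-stage rule against the t-test gave 43 vs 42%, 74 vs 71% and 96 vs 96% (mean 14), and 43 vs 42%, 71 vs 71% and 95 vs 95% (mean 18). The rise in Step 3 rests on assumed shapes and is largest with unequal group sizes.
- **The Poisson change is a separate step.** A reader might infer that Shapiro-Wilk led to it. The closing paragraph of section 3.6 attributes it to the outcome distribution and names no normality test. It shares the distribution-led logic, but deleting the Shapiro-Wilk sentence would not undo it.
- **Part of the remedy is already in the plan.** The random intercept per cluster is there. The comparison of change by mixed model is worded as optional, however, and the outcome distribution is left open.
- **An analysis plan may settle the test.** That is possible, but the article itself affirms a data-driven choice.

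**Conclusion.** The point holds in limited form. The article leaves the test and effect measure for PSS and BRS to the observed distribution, with Shapiro-Wilk as the only criterion given. For a 0–40 integer score that criterion mainly reflects sample size and mild skew: 21% to 92% switching between 25 and 200 per group at skew 0.43.

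The main consequence is an effect measure that can differ between time points or scales. Type I error is not materially affected when group shapes match. When they differ, a rank result can mislead about means (6.0% to 10.4% rejection at equal means under the shapes assumed here). Differing shapes are plausible for practitioners who volunteer through a yoga school against friends they nominate, and less so between the two randomised control arms.

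Means, SDs, shapes, sample sizes and the either-group rule are assumptions. BRS was not simulated; the point about its effect measure rests on the wording. Because the 12-week data have been reviewed, an analysis fixed now cannot be called prespecified.

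**What to change.** 1. Remove normality testing as the selector of outcome tests. Shapiro-Wilk may stay for choosing descriptive summaries.
2. Name one mean-difference analysis for PSS and BRS at each time point: the mixed model with the cluster random intercept already proposed in Aim 1, with standard errors that are robust at cluster level. Step 4 shows why the robust standard error is needed.
3. Keep rank-based tests as sensitivity analyses only.
4. Adjust for the baseline score in the randomised Simha Kriya versus placebo comparison. Do not require it for the practitioner comparison. That comparison is not randomised, and practitioners' baseline scores may already carry the effect of earlier practice. The Discussion takes this view when it calls a baseline comparison sufficient to show effectiveness.
5. Report this analysis beside the Poisson regression, and label that regression and any other distribution-driven choice as post hoc. With the usual log link, Poisson gives a ratio of means, a third effect measure, so the scale of each result should be stated.

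The cost is wording and a re-analysis of data already collected. No new data or participants are needed.
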